## Abstract

**Background:**

Achieving control of hypertension prevents target organ damage at both the micro and macrovascular level and is a highly cost effective means of lowering the risk for heart attack and stroke particularly in people with diabetes. Clinical trials demonstrate that blood pressure control can be achieved in a large proportion of people. Translating this knowledge into widespread practice is the focus of the Hypertension Management Initiative, which began in 2004 with the goal of improving the management of this chronic health condition by primary care providers and patients in the community.

**Methods:**

This study will test the effect of a systems change on the management of high blood pressure in real world practice in primary care in Ontario, Canada. The systems change intervention involves an interprofessional educational program bringing together physicians, nurses and pharmacists with tools for both providers and patients to facilitate blood pressure management. Each of two waves of subjects were enrolled over a 6 month period with the initial enrollment between waves separated by 9 months. Blood pressure will be measured with the BpTru ^® ^automated blood pressure device. To determine the effectiveness of the intervention, a before and after analysis within all subjects will compare blood pressure at baseline to annual measurements for the three year study. To assess whether the intervention has an impact on blood pressure control independent of community trends, a betwen group comparison of baseline blood pressures in the delayed wave will be made with the immediate wave during the same time period, so that the immediate wave has experienced the intervention for at least 9 months. The total enrollment goal is 5,000 subjects. The practice locations include 10 Family Health Teams (FHTs) and 1 Community Health Centre (CHC) and approximately 49 primary care physicians, 15 nurse practitioners, 37 registered nurses and over 150 community pharmacists across the 11 communities throughout the province of Ontario. The 11 primary care sites will be divided into immediate and delayed groups based on geography and the use of an electronic versus a traditional chart patient record.

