#### Rationale for the Evaluation Design

The reasoning for this delayed approach is that it helps to minimize the potential for threats to internal validity, which are defined as alternate explanations for outcome results other than the impact of the intervention itself. The inclusion of the delayed group controls for outside influences that may occur over time such as educational materials, new research results relating to hypertension or the release of new clinical practice recommendations.

As shown in the timeline (Table 3), the immediate intervention sites will receive the intervention over a 9 month period between Time 2 and 3, including the workshop and all tools developed, whereas the delayed intervention sites will not begin receiving the intervention until Time 3. Thus, between Time 2 and Time 3, it is hypothesized that healthcare providers in the immediate intervention sites will begin to use the tools developed by HSFO and to optimize their management of hypertensive patients. Healthcare providers in the delayed intervention sites will not have received the intervention and are expected to continue with treatment as usual. It is planned that blood pressure measurements will be conducted at Time 3 for patients in both the immediate intervention (after 9 months of the intervention) and delayed intervention (at their baseline) sites. Since the patients in the immediate intervention sites will have been enrolled nine months earlier, it is expected that their blood pressures in follow up visits will be better controlled (due to improvements in provider hypertension management practices stemming from their participation in the initiative and usage of tools developed) than those of their counterparts in the delayed intervention sites who will be providing their baseline BP reading at Time 3 when they are prepared to start the intervention.

**Table 3 T3:** HMI Beta Phase Evaluation Timeline

	**Time 1**	**Time 2**	**Time 3**	**Time 4**	**Time 5**

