After patient information is entered into the dataset, monthly and quarterly confidential practice audit reports will be available to all practitioners on the secure website linked to the web-based dataset. Moreover, the practitioner will be able to access the data set at anytime and generate ad hoc "drill-down" reports on his/her patients only. While the same practitioner can compare aggregate data from different sites, he/she cannot access the individual patient information of another physician. The web-based dataset will generate regular confidential practice reports based on the data submitted, for each participating physician and nurse practitioner, comparing the practice to that of other providers at the same site and to those of the other sites and participating healthcare providers. Reports are also generated at a site level for the other healthcare providers to access.

The web-based dataset will be hosted on a Personal Health Information Protection Act (PHIPA) compliant server provided by the dataset developer.

The patient will also be offered the patient toolkit, including the "Take the Pressure Off" patient book. This patient resource provides information and education on hypertension, its risk factors, lifestyle change information, and lists other resources. The Patient-Provider Agreement will be reviewed and completed, including the BP goal, the patient's selected lifestyle risk factor which (s)he wishes to focus on in the coming months/years and the patient's personal plan of action for this selected lifestyle risk factor. The Patient-Provider Agreement is incorporated into the "Take The Pressure Off". The BP goal and patient selected lifestyle risk factor is also documented in the HBP Registration (baseline) and Flow sheet (follow-up) data forms.

In order to assess the impact of the Hypertension Management Initiative on both healthcare provider practice patterns and patient blood pressure readings and control, it is necessary to compare data from the pre-program period to the program period. In order to assess any changes from before to after the intervention, a combination of chart reviews, for the pre-program period, and the web-based patient dataset, for the program period, will be used. Thus, data about the practice patterns of individual healthcare providers and their individual patients' blood pressure data will be used as their own comparators pre-intervention versus post-intervention.

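### The plan determines effectiveness from an uncontrolled before-after change and keeps the concurrent immediate-versus-delayed contrast for a separate question

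*Protocol article*

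**What the plan says.** The abstract's Methods paragraph sets out two analyses with two purposes.

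- Effectiveness: "To determine the effectiveness of the intervention, a before and after analysis within all subjects" sets the baseline reading against annual readings over the three study years. All subjects contribute and no comparator is named.
- Trend: the next sentence begins "To assess whether the intervention has an impact on blood pressure control independent of community trends", and for this purpose a "comparison of baseline blood pressures in the delayed wave will be made with the immediate wave during the same time period".

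Implementation of Toolkit and Interventions repeats the within-subject approach. Pre-programme data come from chart review and programme data from the web dataset, and providers' practice patterns and patients' blood pressures "will be used as their own comparators pre-intervention versus post-intervention".

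Rationale for the Evaluation Design explains why there is a delayed group: "The inclusion of the delayed group controls for outside influences that may occur over time". It places the comparison at Time 3, when immediate sites have had nine months of the programme and delayed patients give their first study reading. Regression to the mean is not mentioned anywhere in the article.

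**The concern.** The design was chosen to guard against explanations other than the programme, yet the analysis that carries the word effectiveness does not use that guard. A fall from baseline to an annual visit contains the programme effect, any secular change (the article itself expects new research and new recommendations) and any regression to the mean.

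The two analyses can disagree. If the before-after fall were significant and the between-group contrast were null, the wording as it stands would still allow the programme to be reported as effective. The annual time points make this worse. The nominal untreated window is the nine months between Time 2 and Time 3. After that the delayed sites start too, so most of the before-after evidence comes from times with no untreated comparator.

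**Working it through.** **1. The plan's own figure.** Statistical Design and Analysis gives 337 per group for a 5 mmHg difference at alpha 0.05, two-sided, and cites an alpha-phase SD without stating its value. It states both power 0.9 and beta 0.20, which cannot both hold, so 337 cannot be reproduced directly. The SD can only be solved back from n = 2·SD²·(z for alpha + z for power)²/5²:

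- Power 0.90: SD = 5·√(337/2)/(1.960 + 1.282) = 20.0 mmHg.
- Power 0.80: SD = 5·√(337/2)/(1.960 + 0.842) = 23.2 mmHg.

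SD 20 is used below. It is an assumption.

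**2. How small a drift would look significant.** Assume no programme effect, a common fall of b mmHg from any other cause, and a baseline-to-follow-up correlation r of 0.5 to 0.7 (not in the documents). The SD of change is 20·√(2(1−r)), which is 20.0 at r = 0.5 and 15.5 at r = 0.7. With N = 5,000 the standard errors are 20.0/√5000 = 0.283 and 15.5/√5000 = 0.219. The probability of p<0.05 is approximately Φ(b/SE − 1.96):

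| N | b (mmHg) | r = 0.5 | r = 0.7 |
|---|---|---|---|
| 5,000 | 1 | 0.94 | 0.995 |
| 5,000 | 2 | 1.00 | 1.00 |
| 337 | 2 | 0.45 | 0.66 |

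This treats patients as independent and assumes no loss to follow-up. Variation between sites in the change would lower these probabilities.

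**3. How large regression to the mean could be.** If patients enter because the baseline reading itself exceeds a cut-off c (in SD units), the expected fall with no treatment effect is SD·(1−r)·φ(c)/(1−Φ(c)). With SD 20 and r from 0.8 down to 0.5:

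- No selection on the baseline reading: 0 mmHg.
- Top 75% selected (φ(c)/(1−Φ(c)) = 0.424): 1.7 to 4.2 mmHg.
- Top 50% selected (ratio 0.798): 3.2 to 8.0 mmHg.

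With SD 23.2 the top-50% range is 3.7 to 9.3 mmHg. The article does not give the entry criteria, so it does not show which line applies.

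**4. What the baseline reading is.** Patient Recruitment Strategy and Consent has providers identify eligible patients shortly before the workshop and measure them at a later appointment. If selection rests on an earlier reading and the correlation between any two visits is constant, the regression has already occurred by the BpTRU baseline. The expected further fall is then zero.

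**5. Does the planned Time 3 contrast escape the problem?** Not entirely. Immediate patients are read at follow-up and delayed patients at enrolment. If entry depends on the enrolment reading, regression to the mean has already lowered the first group and not the second, which favours the programme.

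**The case against.** The strongest reply is that the article already deals with trend. The sentence after the effectiveness sentence plans a concurrent comparison for exactly that purpose, and the rationale section gives the delayed group that role. The design is named as a delayed intervention design, the directional hypothesis is stated for immediate versus delayed at Time 3, and the sample size is per group with a two-sample test. Pre-recruitment and pre-workshop readings are collected in both groups, and significant baseline differences are to be taken into account. How the analyses rank may be settled in an analysis plan that is not shown.

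This disposes of a stronger reading that a reader might infer: that the delayed group goes unused and trend is simply counted as programme effect across the whole evaluation. The documents do not support that.

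A reader might also infer that a regression of several mmHg is to be expected. That is not supported either. The baseline is taken after identification, the criteria are not shown, and in the alpha phase 25% of non-diabetic and 46% of diabetic patients were already controlled before the programme, which does not suggest entry on a high reading alone.

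What the reply does not answer is the label. The article ties the determination of effectiveness to the uncontrolled analysis, and the Implementation section repeats the own-comparator approach. An unseen plan may rank the analyses differently, but this text is what a reader will hold the trial to.

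**Conclusion.** The point holds as one about which analysis carries the conclusion. The before-after change cannot by itself show effectiveness, and at the planned enrolment a drift of 1 to 2 mmHg would probably be significant, given SD 20, correlation 0.5 to 0.7 and independent patients. This does not depend on regression to the mean being large, because a slight secular drift is enough. The contribution of regression to the mean cannot be sized from the article: it runs from near zero to about 3 to 8 mmHg, and the upper range applies only if entry depends on a high reading at the baseline visit. The article should be changed, but it does not follow that the evaluation lacks a control.

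**What to change.** In the abstract's Methods paragraph and in Implementation of Toolkit and Interventions, state that:

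- the test of effectiveness is the immediate-versus-delayed contrast at Time 3, with the pre-programme (Time 1) chart reading as the starting value in both groups and site as the cluster;
- the within-subject change to annual visits is descriptive and does not by itself show effectiveness.

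Acknowledge two limits of the controlled contrast. First, regression to the mean may not cancel: the groups are identified about nine months apart, so the lag from Time 1 to selection differs, and at Time 3 one group is at follow-up and the other at enrolment. Second, Table 3 shows sphygmomanometer readings at Time 1 and BpTRU afterwards, so the device shift cancels only if it is the same in both groups.

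The data are already planned, so only wording and analysis change. The price is precision and reach. As an illustration, take an equal split of 2,500 patients per group over an average of 5.5 sites (about 455 per site) and an assumed intracluster correlation of 0.01 to 0.05. The design effect 1 + (455 − 1)·ICC is then about 5.5 to 23.7, which leaves an effective 452 to 106 patients per group before any gain from adjusting for the Time 1 reading. The controlled evidence covers only about the first nine months; later annual results remain uncontrolled and should be described that way.

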**Improved control of blood pressure among patients reached**
◦ Reduced blood pressure readings of hypertension patients
◦ Increased proportion of patients with hypertension with blood pressure controlled to target
◦ Improved adherence of hypertension patients to prescribed hypertension medication(s)
◦ Improved adherence of high blood pressure/hypertension patients to their selected lifestyle changes

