### Statistical Design and Analysis

The standard deviation used to calculate sample size is derived from results of the alpha phase. In order to have power of 0.9 to detect a difference of 5 mmHg with beta = 0.20 and alpha = 0.05, 337 patients would be required in each group.

Descriptive statistics will be calculated for all variables of interest. Continuous measures will be summarized using means and standard deviations whereas categorical measures were summarized using counts and percentages. For univariate analyses, two sample two-sided t tests will be using for continuous data, whereas chi-square analyses (or Fisher's exact tests in the case of cell sizes) will be used for categorical data. Regression analyses will be constructed from covariates known to impact on blood pressure. All analyses will be carried out using SAS Version 9.1 (SAS Institute, Cary, NC, USA).

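### Effectiveness is tied to an uncontrolled before-after comparison, which is neither the contrast that was sized nor the one that can separate the intervention from time trends

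*Protocol article*

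**What the plan says.** The Abstract (Methods) gives two blood pressure comparisons, each with its own job. The first is said to settle effectiveness: "To determine the effectiveness of the intervention, a before and after analysis within all subjects will compare blood pressure at baseline to annual measurements". The second is there to remove community trends: "To assess whether the intervention has an impact on blood pressure control independent of community trends, a betwen group comparison of baseline blood pressures", taken in the delayed wave and set against the immediate wave in the same period, when the latter has had at least 9 months of the intervention.

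Rationale for the Evaluation Design argues only from the second. It includes the delayed group so that educational materials, new research or new practice recommendations arriving during the study are not mistaken for an effect of the program, and it sets the comparison at Time 3.

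Statistical Design and Analysis also has two groups in mind: "to detect a difference of 5 mmHg with beta = 0.20 and alpha = 0.05, 337 patients would be required in each group". It does not say whether the 5 mmHg is systolic or diastolic, and it does not print the SD, which it says comes from the alpha phase.

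Implementation of Toolkit and Interventions adds a further before-after comparison. To assess impact, "it is necessary to compare data from the pre-program period to the program period", with chart reviews supplying the earlier period and providers and patients serving as their own comparators.

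Table 2 lists "Reduced blood pressure readings of hypertension patients" and "Increased proportion of patients with hypertension with blood pressure controlled to target" side by side. Neither is marked as primary.

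**The concern.** The sentence in the Abstract that says how effectiveness will be determined points to the analysis that cannot attribute a change to the intervention. The protocol itself names influences that could move blood pressure over three years without the program, and it built a delayed group to deal with them. A before-after change in all subjects contains those influences, together with any regression to the mean after enrolment. With thousands of patients it will also be statistically significant for a very small average change.

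The two comparisons can therefore disagree. Blood pressure may fall from baseline in everyone while immediate and delayed sites look alike at Time 3. Followed as written, the plan would then report the initiative as effective on the strength of the weaker comparison, and a result that may reflect only a trend would inform decisions on wider adoption.

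**Working it through.** **1. The stated comparisons side by side.**

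| Comparison | Where | Stated role | Concurrent control | Sample size given |
|---|---|---|---|---|
| Baseline vs annual, all subjects | Abstract, Methods | determines effectiveness | no | no |
| Immediate vs delayed at Time 3 | Abstract; Rationale for the Evaluation Design | effect apart from community trends | yes | yes, 337 per group |
| Pre-program charts vs program data | Implementation of Toolkit and Interventions | impact on practice patterns and blood pressure | no | no |

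**2. What the 337 belongs to.** Inputs: difference 5 mmHg, alpha 0.05 and two-sided two-sample t tests, all from Statistical Design and Analysis. The SD is not printed, so it has to be assumed. The formula per group is n = 2 × (z for alpha + z for power)² × SD² / difference².

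- Power 0.90, assumed SD 20: 2 × (1.960 + 1.282)² × 400 / 25 = 336.2, rounded up to 337. This matches the plan's figure.
- Power 0.80, SD 20: 2 × (1.960 + 0.842)² × 400 / 25 = 251.2, rounded up to 252.
- Solved backwards from 337, the SD is 20.0 at power 0.90 or 23.2 at power 0.80.

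Both powers are shown because the sentence pairs them inconsistently: "power of 0.9 to detect a difference of 5 mmHg with beta = 0.20". That is a separate error. With either power, the figure is for two groups and a difference in means, and the before-after analysis has no sample-size basis in the article.

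**3. How easily the before-after test becomes significant.** Inputs: 5,000 patients (enrolment goal in the Abstract), a mean change of 1 mmHg from any cause, and an assumed SD of change of 15 to 20 mmHg, which the article does not give. Test: paired, two-sided 0.05, patients treated as independent. The probability of significance is approximately Φ(1 × √n / SD − 1.96).

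| n | SD of change | √n / SD | Probability |
|---|---|---|---|
| 5,000 | 15 | 4.71 | 0.997 |
| 5,000 | 20 | 3.54 | 0.942 |
| 2,500 | 15 | 3.33 | 0.915 |
| 2,500 | 20 | 2.50 | 0.705 |

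**4. The between-group test in the same situation.** If a community trend moves both waves by the same 1 mmHg, the expected difference at Time 3 is 0. Leaving clustering and group imbalance aside, that test is then significant only at its nominal 5%. The before-after test would be positive and the between-group test usually null, with no effect of the intervention.

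**5. Multiplicity, conditionally.** Suppose one outcome were tested on four contrasts (three annual changes and one between-group), each at two-sided 0.05, and any one significant result counted as success. If independent, the chance of at least one false positive is 1 − 0.95⁴ = 0.185. Simulation with equal correlation between the tests gives 0.156 at 0.5 and 0.114 at 0.8.

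**The case against.** The best defence is that the two comparisons answer complementary questions. The Abstract uses the before-after analysis to describe change under the program and the delayed wave to remove community trends, so a reader could combine them sensibly. A ranking of endpoints and rules for multiplicity are also commonly left to a full protocol or analysis plan, and neither is shown here. The second half of this stands: the lack of a ranking in Table 2 is not a fault in an article. The first half does not remove the conflict, because the Abstract attaches the determination of effectiveness to the uncontrolled analysis, while the design rationale and the sample size point to the other.

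A reader might go further and infer that the plan carries a false-positive risk of about 32%. That figure comes from 12 tests (systolic, diastolic and control to target, each on four contrasts) at an assumed correlation of 0.5. The document does not support it:

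- It states no rule that any one positive result suffices.
- It gives alpha 0.05 only in the sample-size sentence.
- It does not say that each year is tested separately; one repeated-measures analysis would fit the wording.
- It does not list diastolic pressure as an outcome in its own right. Systolic and diastolic appear together as flow-sheet variables.
- The 32% also counts results in the unfavourable direction. Counting favourable results only, the same grid gives about 16%.

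It is also fair to say that the 1 mmHg calculation concerns bias in an uncontrolled contrast. It is no evidence about multiplicity and is not used as such here.

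**Conclusion.** The point holds as a mismatch within the printed text. Effectiveness is said to be decided by a comparison that has no concurrent control and no sample-size basis, while the comparison that was justified and sized is given a different job. At the planned enrolment, a mean change of 1 mmHg from any cause would make the before-after test significant with probability about 0.94 to 1.00. At half that enrolment the figure is 0.71 to 0.92. These values rest on an assumed SD of change of 15 to 20 mmHg and ignore clustering within sites.

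No family-wise error rate can be attributed to the plan. All that can be said is conditional: if any one of several unadjusted 0.05 tests counted as success, the error would exceed 5%, for example about 0.11 to 0.185 for four contrasts on one outcome.

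The between-group contrast has limits of its own. Only 11 sites are involved and they are assigned manually, so clustering and non-random assignment remain. It also sets patients at enrolment against patients in follow-up, so it deals with calendar-time trends but not necessarily with regression to the mean after enrolment.

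**What to change.** Three changes of wording, in the Abstract and in Statistical Design and Analysis:

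1. State that the conclusion on effectiveness rests on the comparison of immediate with delayed sites at Time 3.
2. State which blood pressure measure the 5 mmHg refers to, namely the one whose alpha-phase SD was used, and make it the primary endpoint.
3. Label the annual before-after comparisons and the chart-to-program comparison as supportive, and make Implementation of Toolkit and Interventions agree.

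No patients, visits or data are added. The cost is that a significant before-after change on its own can no longer support a claim of effectiveness. The site-level problems noted in the verdict need their own treatment in the analysis.

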**Immediate Intervention**	*Measurement:* • BP readings (sphygmom.) • site characteristics • practice patterns re. HTN management	*Receive intervention*: • workshop • tools enrolment of patients *Measurement*: • baseline BP readings (BpTRU)	(continue to receive site support for intervention) *Measurement*: • follow up visit • BP readings (BpTRU)	(continue to receive site support for intervention) *Measurement:* • follow up visit • BP readings (BpTRU)	*Measurement:* • follow up visit • BP readings (BpTRU) • practice patterns re. HTN management

**Delayed Intervention**	*Measurement*: • BP readings (sphygmom.) • site characteristics • practice patterns re. HTN management	treatment as usual	*receive intervention:* • workshop • tools enrolment of patients *measurement*: • baseline BP readings (BpTRU)	(continue to receive site support for intervention) *Measurement:* • follow up visit • BP readings (BpTRU)	*Measurement:* • follow up visit • BP readings (BpTRU) • practice patterns re. HTN management

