Demographic and baseline data will be compared between the immediate intervention and delayed intervention groups to determine if the groups did differ significantly in terms of healthcare provider practice patterns, site characteristics, and patient blood pressure control before the implementation of the program. If any statistically significant differences are detected between immediate intervention and delayed intervention groups, then these will be taken into account in analyses following the immediate intervention. The immediate intervention group will have the intervention for a longer duration than the delayed intervention group, providing an opportunity to determine whether there is a "dosage effect" associated with having the immediate intervention for a longer time period.

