Given that HSFO approached this particular group of health care providers to participate in a program relating to hypertension, this may have heightened their awareness of the issue and affected their management of patients with hypertension (in addition to the influence of the intervention itself). This phenomenon in which subjects of research may be affected by the knowledge that they are subjects of research is known as the Hawthorne Effect. For this reason, data will be collected from both the immediate intervention and delayed intervention groups pertaining to office visits conducted during the six months prior to initial contact with sites for recruitment into the initiative as well as data from office visits after first contact but before the site initiation workshop. Gathering this data will allow an assessment of practice patterns for these groups between the pre-recruitment period and the period following recruitment, which may relate to the Hawthorne Effect. As well, this will allow comparisons to be made between the immediate intervention and delayed intervention groups in terms of patient blood pressure readings as well as healthcare provider practice patterns.

In the patient consent form, patients are informed that information from their medical chart may be collected in order to evaluate the education and tools provided to themselves and their health care provider, and that all information collected would be kept strictly confidential and would be grouped for analysis. All participating and nurse practitioners have provided written consent to a chart review with the intent to evaluate the education and tools provided to the healthcare providers.

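### The only controlled comparison sets follow-up BP against enrolment BP in hand-assigned sites, and pre-program BP enters it only if a weak significance test flags a difference

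*Protocol article*

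**What the plan says.** The Abstract (Methods) names two effectiveness analyses. One is an uncontrolled before-after comparison within all subjects. The other is the between-group "comparison of baseline blood pressures in the delayed wave will be made with the immediate wave during the same time period", meant to show an effect independent of community trends.

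Rationale for the Evaluation Design repeats the second: Time 3 measurements are planned "for patients in both the immediate intervention (after 9 months of the intervention) and delayed intervention (at their baseline) sites", and the delayed patients are those "who will be providing their baseline BP reading at Time 3 when they are prepared to start the intervention". It adds: "The inclusion of the delayed group controls for outside influences that may occur over time".

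Table 3 shows the same layout. At Time 3 the immediate group has a follow-up visit and the delayed group has enrolment, both on BpTRU. At Time 1 both groups have readings on another device, entered as "BP readings (sphygmom".

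Evaluation Design gives 6 immediate and 5 delayed sites. The section on assignment to groups says sites are allocated manually. It plans to compare the groups on provider practice patterns, "site characteristics, and patient blood pressure control before the implementation of the program", and then sets the rule: "If any statistically significant differences are detected between immediate intervention and delayed intervention groups, then these will be taken into account in analyses".

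Implementation of Toolkit and Interventions confirms that pre-program data will exist in both groups: "data will be collected from both the immediate intervention and delayed intervention groups pertaining to office visits conducted during the six months prior" to first contact with the sites. It also plans to use patients' own pre-program readings as comparators.

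Statistical Design and Analysis names two-sample t tests, and regression on covariates known to affect blood pressure.

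**The concern.** Two features of the Time 3 contrast have nothing to do with the program.

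- **Site mix.** With 11 sites placed by hand, a lasting difference in blood pressure between the two sets of sites goes into a comparison of levels. The protection is a rule that adjusts only when a significance test is positive. With 6 against 5 sites, a negative test says little about whether the groups are alike.
- **Visit type.** Immediate patients are returning about 9 months after enrolment, while delayed patients are giving their first BpTRU reading. Familiarity with the procedure, regression to the mean and selective return could each lower readings in the immediate group alone. A delayed group can absorb influences that act on both groups over time, but not an effect present in only one of them.

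The other effectiveness analysis has no control, so the claim of an effect beyond community trends rests on this contrast. It could show a difference with no program effect, or hide a real one.

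**Working it through.** **1. The plan's own figure.** The article gives a 5 mmHg difference, alpha 0.05, power 0.9 and 337 patients per group, but no SD. Two-sided, n = 2 × SD² × (1.960 + 1.282)² / 5². With SD = 20 this is 2 × 400 × 10.51 / 25 = 336.2, rounded up to 337. So SD = 20 is the value implied at power 0.9, and it is used below as an assumption. (The same sentence gives beta = 0.20, which contradicts power 0.9. On that reading the implied SD is about 23.2.)

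**2. How far apart the groups could be from sites alone.** No ICC is given, so a range is assumed. The SE of the group difference from sites alone is SD × √ICC × √(1/6 + 1/5), and √(1/6 + 1/5) = 0.6055.

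| ICC (assumed) | Between-site SD | SE of 6-vs-5 difference | 95% limit (1.96 × SE) |
|---|---|---|---|
| 0.01 | 2.00 | 1.21 | 2.4 mmHg |
| 0.02 | 2.83 | 1.71 | 3.4 mmHg |
| 0.05 | 4.47 | 2.71 | 5.3 mmHg |

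These are 95% limits under chance assignment, not expected imbalances. At ICC 0.02 the mean absolute imbalance is about 1.71 × 0.80 = 1.4 mmHg.

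**3. How often the significance screen would miss a difference.** Take a t test on 11 site means (9 df), with 5,000 / 11 ≈ 455 readings per site. This is an assumption, since the article does not say how many Time 1 readings will be reviewed. SE = √[400 × (ICC + (1 − ICC)/455) × (1/6 + 1/5)]. Power is from the noncentral t distribution.

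| ICC (assumed) | SE | Detects 3 mmHg | Misses 3 mmHg | Detects 5 mmHg |
|---|---|---|---|---|
| 0.01 | 1.34 | 0.52 | 48% | 0.91 |
| 0.03 | 2.17 | 0.24 | 76% | 0.54 |
| 0.05 | 2.76 | 0.16 | 84% | 0.37 |

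**4. What an offset does to the Time 3 test.** Suppose no program effect, SD 20 and patients treated as independent. A non-program offset b, from site mix or visit type, gives a significant result with these probabilities:

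| Patients (immediate / delayed) | SE | b = 1 | b = 2 | b = 3 | b = 5 |
|---|---|---|---|---|---|
| 337 / 337 | 20 × √(2/337) = 1.54 | 0.10 | 0.26 | 0.50 | 0.90 |
| 2,727 / 2,273 | 20 × √(1/2727 + 1/2273) = 0.57 | 0.42 | 0.94 | 1.00 | 1.00 |

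The second row splits the 5,000 enrolment goal 6:5 by sites (assumed). Enrolling more patients does not shrink the offset; it only makes it more likely to be declared significant.

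**5. Visit type.** No arithmetic is possible, because the article gives no size for a first-to-repeat-visit fall. Any such fall adds one for one, so each 1 mmHg is 1/5 = 20% of the target difference.

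**The case against.** The strongest reply is that pre-program blood pressure is used. The section on assignment compares it between groups and provides for adjustment, and Implementation of Toolkit and Interventions uses it within patients and between groups. This stands. A reader might infer that Time 1 readings are ignored and that every site difference is booked as program effect, but the documents do not support that. The fault is that use in the controlled comparison is conditional.

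The screen might also be run on patients, not sites. By the arithmetic of step 4, a 3 mmHg difference would then be flagged about half the time at 337 per group and almost always at 5,000. That ignores site, so it would also flag ordinary site variation, and the way of taking a flagged difference into account would still be unnamed.

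A reader might further infer that regression to the mean and drop-out are shown to favour the program. They are not. The eligibility criteria are not in the article, and providers pick eligible patients before the workshop, so the enrolment reading is not shown to be the selecting one. Enrolment visits also follow the workshop, so delayed baselines may already reflect trained providers, which would work against the program.

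The claim made for the delayed group concerns influences over time, and a concurrent comparison does address shared trends. Manual assignment aims at balance on geography and record type, so the chance limits in step 2 are only a guide.

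Finally, model detail may sit in an analysis plan not shown, and the regression covariates do not exclude prior blood pressure. But the significance trigger and the Time 3 contrast are written down here as rules, not left open.

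**Conclusion.** The concern holds in this form. The controlled comparison sets Time 3 follow-up readings against enrolment readings across 11 manually assigned sites, and Time 1 blood pressure enters only after a positive significance test. A site-level test would miss a true 3 mmHg difference about 48% to 84% of the time, and that difference would stay in the estimate in either direction. The figures assume SD 20 (inferred from 337 per group), ICC 0.01 to 0.05 and about 455 Time 1 readings per site; the article states none of these.

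The mismatch in visit type is unaddressed. It may favour the program, but neither its size nor its direction can be shown from the article.

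**What to change.** **Change the rule.** Drop the significance trigger and always use Time 1 blood pressure in the controlled comparison. Either of these would do:

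- a difference-in-differences (group-by-period term): Time 3 minus Time 1 in the immediate sites, less the same change in the delayed sites;
- the Time 3 comparison with Time 1 blood pressure as a covariate.

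Fit it with random site, site-by-period and patient effects, or run an equivalent site-level analysis. Without the site-by-period term, the model assumes that all sites drift alike and can understate the standard error.

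**State what this does not cure.** The move from sphygmomanometer to BpTRU cancels only if the shift is equal in both groups. The first-visit and retention asymmetry remains, because the delayed Time 3 reading is still an enrolment reading. Report it as a limitation and gauge it with data already planned, for example by comparing Time 2 enrolment readings in the immediate sites with Time 3 enrolment readings in the delayed sites. Those are like visits, so a gap there reflects site mix and the intervening trend. This is a partial check: it does not by itself separate a first-to-repeat-visit fall from a program effect.

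**Sensitivity analysis.** Repeat the analysis in patients whose hypertension was already charted at Time 1. This should not be the main analysis, because it removes patients diagnosed later, and time to diagnosis is a listed indicator in Table 2.

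**Cost.** Mainly analysis wording, since Time 1 readings are already planned in both groups. Patients without a Time 1 reading drop out of this model. Precision may fall if the Time 1 to Time 3 correlation is low: a change score has patient-level variance 2 × SD² × (1 − correlation), which exceeds SD² when the correlation is below 0.5.
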